## Abstract

**Background:**

Colon cancer treatment is dependent on the stage at diagnosis. The current Tumor-Node-Metastasis (TNM) staging for the selection of patients for adjuvant chemotherapy needs additional prognostic and predictive biomarkers. Better decision making for chemotherapy will result in reducing over- and undertreatment. We developed a new, easy-to-apply, practice-changing method to select colon cancer patients for adjuvant chemotherapy: the tumor-stroma ratio (TSR). The TSR distinguishes within stage II-III patients who will likely benefit from adjuvant chemotherapy and those who will not.

**Objective:**

The aim of the study was to add, in addition to the TNM classification, the TSR to current routine pathology evaluation. Pathologists will be instructed for scoring the TSR in combination with a quality assessment program. An international multicenter study will validate the parameter prospectively.

**Methods:**

The study is designed for future implementation of the TSR to the current TNM guidelines, using routinely Haematoxylin- and Eosin-stained tumor tissue sections. In part 1 of the study, an electronic learning (e-learning) module with a quality assessment program using the European Society of Pathology framework will be developed. This module will be used to assess the reliability and reproducibility of the TSR, conducted by national and international pathologists. Part 2 will involve the validation of the TSR in a prospective cohort of colon cancer p-stage II-III patients in a multicenter setting. In total, 1500 patients will be included.

**Results:**

The results of part 1 will be expected in the first half of 2019. For part 2, the inclusion of patients in the prospective study, which started at the end of 2018, will take 3 years with an additional follow-up after another 3 years.

**Conclusions:**

The main endpoints of this study are as follows: in part 1, trained (international) pathologists who are able to reliably score the TSR, resulting in low intra- and interobserver variation; in part 2, confirmation of significant survival differences for patients with a stroma-high tumor versus patients with a stroma-low tumor. On the basis of these findings, a modification in current treatment guidelines will be suggested.

**Trial Registration:**

Netherlands Trial Register NTR7270; https://www.trialregister.nl/trial/7072

**International Registered Report Identifier (IRRID):**

DERR1-10.2196/13464

## Introduction

### Background

Despite complete resection of the primary tumor and surrounding lymph nodes, colon cancer patients often develop recurrence of disease, caused by the remaining micrometastases. These can be treated with chemotherapy. However, as micrometastases are difficult to detect, treatment guidelines are usually based on tumor characteristics related to disease progression and survival, such as depth of invasion and lymph node metastasis. The current guidelines advise to give adjuvant chemotherapy to patients with stage III colon carcinoma and patients with stage II and one or more high-risk factors [1]. Only a part of the patients who are treated with chemotherapy will actually benefit. Furthermore, there is also substantial undertreatment because 25% of the stage II patients, who do not receive adjuvant chemotherapy, will develop recurrence or metastasis within 5 years [2]. Some patients with stage IIIA receive adjuvant chemotherapy, whereas in some cases, the prognosis is better compared with patients with stage IIB disease [1]. The selection of colon cancer patients for adjuvant treatment should be further improved to establish an optimal treatment regimen for each patient.

Over the last decade, the microenvironment or stromal (ie, nonepithelial) component of tumors has been studied intensively. There is increasing evidence that the tumor stroma plays an important role in the biological behavior of tumors, their growth, ability to metastasize, but also their response or resistance to anticancer drugs [3-6]. Tumors that are rich in stroma behave in a more aggressive way compared with tumors with little stroma [2,7].

### Tumor-Stroma Ratio

The tumor-stroma ratio (TSR) parameter is based on the amount of stroma within the primary tumor and can be determined, without extra costs, during routine pathology assessment. Using the TSR, stage II/III stroma-high (high-risk) patients can be adequately registered for treatment with chemotherapy, whereas for the (elderly) patients with stage III and stroma-low, further discussion is needed as to whether adjuvant therapy will benefit these patients. New guidelines for patient management will have consequences for better patient management leading to a more optimal selection for adjuvant chemotherapy with a potential reduction in costs.

A high stroma percentage (>50%) is an unfavorable prognostic factor. The TSR has been validated in various international studies with high interobserver agreements [2,7-12]. The TSR was discussed by the TNM Evaluation Committee, the Union for International Cancer Control, and the College of American Pathologists. They stated that our observations are important and novel and have the potential to be added to the TNM staging algorithm as prognosticator. They advocated validation in a prospective multicenter study and development of consensus agreement and a quality assessment program. This protocol elaborates on this recommendation.

### Objectives

The overall objective is the addition of the TSR to current routine pathology next to the TNM classification for clinical decision making.

Primary objective for each part of the project:

Part 1: To evaluate and improve the reliability and reproducibility of pathologists specifically instructed for TSR scoring.Part 2: To confirm the prognostic power of the method to select patients at risk for the development of recurrence of disease resulting in high-level evidence for adaptation of guidelines.

## Methods

### Histopathological Scoring of the Tumor-Stroma Ratio

For the evaluation of the TSR, Haematoxylin and Eosin (H&E)–stained sections of the primary colon carcinoma, used in routine pathology to determine the T-stage (ie, the deepest part of the tumor), are analyzed using conventional microscopy. Areas with the largest amount of stroma are selected using a 2.5x or 5x objective. An area where both tumor and stromal tissue are present within this vision site is selected using a 10x objective. Tumor cells have to be present at all borders of the selected image field. Mucinous tumors, although more difficult, can also be scored; an area containing mucus may be used. However, the volume of mucus should be excluded when determining the TSR. Other challenging cases can be tumors with abundant necrosis and/or muscle tissue in between tumor glands. Necrotic areas or muscle tissue should be avoided in the scoring procedure. It is not necessary to score the TSR at the invasive front, picking a field with as much stroma as possible is more accurate.

Stroma-high is defined as >50% stromal area and stroma-low, as ≤50% stromal area in the histological section (Figure 1). This cut-off has been determined a priori with maximum discriminative power [2,7,9]. Even if there is only one image field with a stroma-high score, this image field is decisive to categorize the patient as stroma-high.

The scoring protocol is available in an instruction movie on the Uniform Noting for International application of the Tumor-stroma ratio as Easy Diagnostic tool (UNITED) study website [13] and in written form published by our group [14].

**Figure 1 figure1:**
[figure not shown]
Examples of stroma-low colon cancer (A) and stroma-high colon cancer (B).

### Study Design

Part 1 will consist of an electronic learning (e-learning) module which has been developed with a quality assessment program in the framework of the European Society of Pathology (ESP) External Quality Assessment program. Using this module, a reliability and reproducibility study on H&E-stained tumor tissues will be conducted among national and international pathologists.

Part 2 will involve validation in a prospective cohort of colon cancer stage II-III patients within this multicenter setting. The inclusion is expected to take 3 years, with a 3-year follow-up period.

### Patient Description

In the UNITED study, all patients are diagnosed with pathological stage (p-stage) II or p-stage III colon cancer. For e-learning, H&E-stained slides of stage II-III colon cancer patients were selected in a retrospective manner. Material was obtained from the archive of the Department of Pathology of the Leiden University Medical Center (LUMC).

### Part 1: The E-Learning Module

An e-learning module has been developed in the framework of the ESP. The software used for the e-learning is PathXL Tutor version 6.1.1.1. (Philips). This is a Web-based software that can be accessed worldwide. Participating pathologists receive specific user credentials for access to the e-learning sets. The workflow is shown in Figure 2 and includes an introduction film with the technical instructions. Hereafter, the participating pathologists may start the e-learning by analyzing the training set containing 40 cases.

TSR scores of participating pathologists will be compared with a reference score (consisting of 3 observers at the LUMC). If a pathologist does not pass a set (interobserver variability kappa<.70), he or she is asked to re-analyze the set. If need be, the instruction video and protocol can be studied again. If a pathologist passes the set (kappa≥.70), the pathologist is able to continue to the next set of 40 slides. The test set will be repeated after 2 months, thereafter inter- and intraobserver variability are determined. The pathologists are unaware of any clinical information or previous scoring.

The quality of TSR scoring by the participating pathologists will be monitored on a yearly basis by offering control series.

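### Part 1 uses the same kappa as pass mark and as outcome, so an interobserver result built on accepted scores would be biased upward

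*Protocol article*

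**What the plan says.** The protocol article, under Part 1: The E-Learning Module, sets out a sequence. First, "the participating pathologists may start the e-learning by analyzing the training set containing 40 cases". Each pathologist's scores are compared with a reference score set by three LUMC observers. Then "If a pathologist does not pass a set (interobserver variability kappa<.70), he or she is asked to re-analyze the set", whereas "If a pathologist passes the set (kappa≥.70), the pathologist is able to continue to the next set of 40 slides". No maximum number of attempts is given. Finally, "The test set will be repeated after 2 months, thereafter inter- and intraobserver variability are determined". The same section adds: "The pathologists are unaware of any clinical information or previous scoring".

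Statistical Analysis, Part 1 names Cohen kappa for both inter- and intraobserver variability. Under Objectives the Part 1 aim is "To evaluate and improve the reliability and reproducibility of pathologists specifically instructed for TSR scoring". The Conclusions of the Abstract give the endpoint as "trained (international) pathologists who are able to reliably score the TSR, resulting in low intra- and interobserver variation".

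**The concern.** One statistic does two jobs. Kappa against the reference decides who proceeds, and kappa is then the measure of how reliable the scoring is. A pathologist below the mark scores the same slides again until the mark is reached, and one who never reaches it on the training set contributes no test-set data.

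The rule is worded for any set, so on its face it applies to the test set too. If the accepted test-set score is what gets reported, the interobserver kappa cannot fall below 0.70, whatever the true agreement.

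This matters because Study Design presents Part 1 as a reliability and reproducibility study as well as a training course, and the Part 2 section treats completion of the e-learning as adequate instruction for routine scoring. An inflated kappa would overstate how well the score transfers to new pathologists. In addition, agreement with a single-centre reference is labelled interobserver variability in the pass rule, while routine use also depends on agreement between the participating pathologists.

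**Working it through.** The article states no expected kappa or sample size for Part 1, so there is no figure to reproduce. The check asks what the pass rule does to an observed kappa.

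**Inputs from the article:** 40 slides per set; pass mark 0.70; repeat on the same set; no stated attempt limit. 
**Assumptions:** binary score (stroma-high or stroma-low); stroma-high share of slides 25%, 32.5% or 50% (the slide mix is not given; the sample size section gives patient shares of 20% to 35%); attempts independent, with no learning.

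**Step 1: one rater, true kappa κ = 0.60.** With stroma-high share p and equal margins, the cell probabilities are: both high p² + κp(1−p); each discordant cell p(1−p)(1−κ); both low (1−p)² + κp(1−p). At p = 0.325 these are 0.237, 0.088, 0.088 and 0.587. Summing the multinomial probabilities of all 40-slide tables with observed kappa ≥ 0.70 gives the chance P of passing. The chance within three attempts is 1 − (1 − P)³.

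| Stroma-high share | Pass, one attempt | Pass within three | Mean kappa when passed |
|---|---|---|---|
| 25% | 23.6% | 55% | 0.78 |
| 32.5% | 21.7% | 52% | 0.77 |
| 50% | 20.6% | 50% | 0.76 |

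For the middle row: 1 − 0.783³ = 0.52. The accepted kappa exceeds the true one by about 0.77 − 0.60 = 0.17.

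**Step 2: sensitivity to the model.** If the number of reference stroma-high slides is held fixed (10, 13 or 20 of 40), passing is slightly easier: 24% to 29% at one attempt, 57% to 64% within three, mean accepted kappa 0.75 to 0.78. The balanced case can be checked by hand. With 20 of 40 stroma-high, expected agreement is 0.5, so kappa = 2 × agreement − 1. Passing needs agreement of 0.85, or 34 of 40. True kappa 0.60 means agreement 0.80, and P(Binomial(40, 0.80) ≥ 34) = 0.286. Within three attempts: 1 − 0.714³ = 0.64.

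**Step 3: a population of raters.** Simulation with true kappa of mean 0.60 and SD 0.10, 32.5% stroma-high, up to three attempts per set:

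| Score used | Mean kappa | Share at ≥ 0.70 |
|---|---|---|
| First attempt, all who start the e-learning | 0.60 | 30% |
| First test-set attempt, training passers | 0.65 | 40% |
| Accepted test-set score, if the test set is gated | 0.79 | 100% |
| 2-month repeat after both gates, repeat not gated | 0.68 | 47% |

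With 20 attempts allowed, the second and fourth rows both fall to about 0.62, because nearly everyone passes and selection fades; the accepted score stays at 0.78. With a true mean of 0.80 (SD 0.08) and three attempts, the four rows are 0.80, 0.80, 0.84 and 0.81.

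**Step 4: reading the table.** The large distortion sits in one row, the accepted score on a gated set. The training gate alone shifts the test-set mean from 0.60 to 0.65. That shift reflects who gets through, since the test slides are a separate set.

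**The case against.** A reader might infer that low interobserver variation is largely guaranteed by the rule. The article does not support that. Variability is determined after the 2-month repeat, to which no pass rule is expressly attached, and ungated scores fall back towards true agreement, so an unfavourable result could still appear. Nor does the article say that first attempts or failures are left out of the report. The workflow figure, which is not shown, may settle which sets are gated. This part of the objection stands and limits the point.

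The training aim also counts. The objective is to improve as well as evaluate, in instructed pathologists, so restricting attention to those who completed training is partly intended. That is a good reason to start from the test set rather than from the first training attempt. It is no reason to use test-set scores accepted only after repetition.

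Two further stronger readings fail. Inflation of the intraobserver kappa by repeat exposure is possible, but the gate concerns agreement with a reference, not self-agreement; a 2-month gap and blinding to previous scoring are specified, and no size can be put on it. It is also not established that the final kappa is against the reference only: the statistical section names no comparator, and a between-pathologist kappa would not be truncated by a gate against the reference.

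Finally, an article may leave analysis sets and intervals to a fuller document. The point does not rest on that silence. It rests on the stated rule, which makes the outcome statistic the condition for leaving a set.

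**Conclusion.** The point holds in a limited form. In Part 1 the outcome statistic is also the progression gate, with repeats on the same slides and no stated limit. If the test set is gated, as the wording literally allows, an accepted interobserver kappa is at least 0.70 by construction, and about 0.17 too high for a rater whose true kappa is 0.60. For scores outside the gate the upward shift is modest: 0.65 to 0.68 against 0.60 with three attempts, smaller with many attempts, and slight if true kappa is near 0.80.

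These sizes rest on assumed true kappas, slide mix and independent attempts. Memory or learning on the same slides would raise the pass rates further. Any effect on intraobserver kappa is unquantified.

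**What to change.** State that the 0.70 mark serves progression and certification only, and say which sets it applies to. Then:

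- Take the interobserver result from the first test-set attempt of every pathologist who starts that set, pass or fail.
- Base intraobserver kappa on that first attempt against the 2-month repeat, without removing those below 0.70.
- Report the number of attempts per set and the number of pathologists who never pass training.
- Report kappa between pathologists beside kappa against the reference, each with a 95% CI.

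The training programme itself is unchanged. First-attempt scores must be retained, which the article does not confirm is done at present, and the two-month repeat must be open to those below the mark. The reported kappa may be less favourable.

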### Part 2: Validation of the Tumor-Stroma Ratio in a Prospective Study

After finishing the e-learning, the pathologist is well instructed to score TSR in the daily routine. To validate the TSR prospectively, a multicenter study is set up. The study aims to include, in the participating centers, a total of 1500 colon cancer patients who have undergone complete curative resection (R0 resection), independent of receiving adjuvant chemotherapy according to actual guidelines.

### Recruitment of Patients and Consent

Each consecutive eligible patient with a clinical stage I/II/III tumor will be informed about the study by their physician or research nurse. After informed consent, the pathologist is notified that the TSR can be determined. All patients, independent of gender and family history, are invited to participate. Medical history is no reason for exclusion, apart from malignancies within 10 years before the current colon carcinoma. Textboxes 1 and 2 describe the inclusion and exclusion criteria.

**Figure 2 figure2:**
[figure not shown]
Flowchart for the instruction of participating pathologists using the e-learning module.

Patient inclusion criteria.Histologically proven colon carcinomaComplete curative resection (R0 resection)Clinical stage I (T1-2, N0, M0), II (T3-4, N0, M0) or III (any T, N1-2, M0)Aged ≥18 yearsWritten informed consent

Patient exclusion criteria.Neo-adjuvant treatment; this influences the amount of tumor and stroma, by fibrosis formationAny malignancy within 10 years before the current colon carcinoma (except for basal cell carcinoma or cervical carcinoma in situ) or any colon carcinoma in history; owing to prolonged treatment or metastasis from earlier primary tumors that can influence the current colon carcinoma prognosis. Basal cell carcinoma and cervical carcinoma in situ do not have metastatic capacityMultiple synchronous colon tumors; patients with synchronous tumors are likely to have a worse prognosis and need a different approach for treatmentRectum tumors; these are defined as separate entities. Prognosis and treatment is different compared with colon tumorsAdditional exclusion after surgery:p-stage I or stage IV; p-stage I is excluded as these patients will not receive adjuvant treatment. Stage IV patients are excluded as these patients are palliatively treatedDeceased within 3 months after surgery; patients who die within 3 months after surgery die most often owing to comorbidity or surgical complications

### Safety Reporting and Risk Analysis

The patient material to be analyzed in this study is a conventional H&E-stained histological section of the primary tumor, obtained during the routine pathology process. The method is without any additional intervention and the study does not have consequences for the treatment of patients. Therefore, the safety or health of participating subjects will not be jeopardized in any way by this study. Consequently, no adverse events, serious adverse events, or suspected unexpected serious adverse events will occur owing to the study. A data safety monitoring board is not indicated.

### Data Storage

The LUMC Datacenter, Department of Surgery, is the Central Datacenter and responsible for supply of electronic Case Report Forms, study database, generation of queries within the database, and central monitoring.

Data will be stored in Castor Electronic Data Capture (Castor EDC; Castor, Amsterdam, the Netherlands) [15]. Castor EDC is a cloud-based electronic data capture platform, easy-to-use by researchers worldwide and highly secured. Data can be easily captured; therefore, data are of high quality and reusable. Data and documents will be stored for at least 15 years.

### Statistical Analysis

Statistical analysis will be performed using IBM SPSS Statistics version 25.0 in collaboration with the Department of Medical Statistics of the LUMC.

#### Part 1

For the analysis of the inter- and intraobserver variability, Cohen kappa coefficient will be used.

#### Part 2

##### Sample Size Calculation

For the prospective cohort, a sample size calculation has been performed for both stages based on earlier research findings [2,7].

p-stage II patients: with a hazard ratio (HR) of 2.0, adjusted for TNM, and a known percentage of stroma-high patients in p-stage II of 20% to 25% [2,7], 114 recurrence events with 90% power are necessary. To achieve 114 recurrence events based on an event rate of 0.0575 per year (leading to a 5-year probability of 75% and 3-year recurrence probability of 84.2%), this leads to 722 patients.p-stage III patients: with an HR of 2.0, adjusted for TNM, and a known percentage of stroma-high patients in stage III of 30% to 35% [2,7], 97 recurrence events with 90% power are necessary. To achieve 97 recurrence events based on an event rate of 0.081 per year (leading to a 5-year probability of 66.7% and 3-year recurrence probability of 78.4%), this leads to 450 patients.

To obtain 1172 evaluable p-stage II/III, approximately 1500 (+25%) patients will be registered, as all p-stage I and stage IV patients will be excluded.

##### Statistical Analysis

Survival analysis will be performed using Kaplan-Meier survival analysis and differences in survival distributions will be tested using Log Rank statistics. The Cox proportional hazard model is used to determine the HR of explanatory variables for overall and disease-free survival (OS and DFS, respectively).

OS is defined as the time period between the date of surgery and the date of death from any cause or the date of the last follow-up. DFS is defined as the time between the date of surgery and the date of any recurrence (local, regional, or distant metastasis), date of new primary tumor, or date of death (any cause). If no event occurs, DFS is calculated as the time period until the date of last follow-up.

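### Part 2 is sized on a TNM-adjusted TSR hazard ratio, but the only test named has no stated stratification or adjustment, and the Cox model is not tied to the success statement

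*Protocol article*

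**What the plan says.** All four places are in the protocol article.

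- **Aim (Objectives).** "The overall objective is the addition of the TSR to current routine pathology next to the TNM classification for clinical decision making". The part 2 objective is to confirm prognostic power for recurrence, as evidence for adapting guidelines.
- **Sizing (Sample Size Calculation).** Each p-stage has its own calculation, both "with a hazard ratio (HR) of 2.0, adjusted for TNM". For p-stage II the result is "114 recurrence events with 90% power are necessary", giving 722 patients. For p-stage III it is "97 recurrence events with 90% power are necessary", giving 450.
- **Analysis (Part 2, Statistical Analysis).** "Survival analysis will be performed using Kaplan-Meier survival analysis and differences in survival distributions will be tested using Log Rank statistics". The next sentence assigns a Cox model to estimate hazard ratios of explanatory variables for OS and DFS. It does not list the variables, mention TNM or say which analysis is primary.
- **Success (Abstract, Conclusions).** The part 2 endpoint is "confirmation of significant survival differences for patients with a stroma-high tumor versus patients with a stroma-low tumor", and a change to treatment guidelines is to be suggested on that basis.

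**The concern.** The aim and the sample size both concern what TSR tells us once TNM is known. A log-rank test without strata or covariates compares stroma-high with stroma-low patients whatever their T and N categories. If stroma-high tumours tend to be more advanced within a stage, that test can be significant when TSR carries no information of its own.

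As written, a significant log-rank result could stand beside an inconclusive adjusted hazard ratio, and nothing in the article says which of them decides. The decision at stake is whether to recommend TSR as an addition to TNM in guidelines.

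**Working it through.** **1. Reproduce the plan's sizing.** Inputs from Sample Size Calculation: HR 2.0, 90% power, stroma-high share 20% to 25% (p-stage II) and 30% to 35% (p-stage III), event rates 0.0575 and 0.081 per year, and 3 years of follow-up. Alpha is not stated; two-sided 0.05 is assumed.

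Events (Schoenfeld) = (1.960 + 1.282)² / [a(1−a)(ln 2)²] = 10.507 / [a(1−a) × 0.4805], where a is the stroma-high share.

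- p-stage II, a = 0.25: 117 (stated 114, within 3%). At a = 0.20: 137.
- p-stage III, a = 0.35: 97 (stated 97). At a = 0.30: 105.
- Patients: 114 / (1 − e^(−0.1725)) = 720 (stated 722); 97 / (1 − e^(−0.243)) = 450 (stated 450).

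The figures come back at the upper end of each share range, from the two-group formula with no allowance for correlation between TSR and TNM. Adjustment therefore enters the sizing only through the assumed HR.

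**2. Bias from mixing stages, if they were pooled.** Suppose TSR has no effect given stage. Take the mid-range shares, 22.5% and 32.5%.

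- Stroma-high: 722 × 0.225 = 162.45 and 450 × 0.325 = 146.25. Mean rate = (162.45 × 0.0575 + 146.25 × 0.081) / 308.7 = 0.0686.
- Stroma-low: 559.55 and 303.75. Mean rate = (559.55 × 0.0575 + 303.75 × 0.081) / 863.3 = 0.0658.
- Spurious HR = 0.0686 / 0.0658 = 1.04.
- With 114 + 97 = 211 events and overall share 308.7 / 1172 = 0.263, the log-rank mean is √(211 × 0.263 × 0.737) × ln 1.0436 = 0.27. The two-sided rejection rate is 5.9%.

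Across the stated share ranges the spurious HR is 1.02 to 1.07 and rejection 5.2% to 7.0%. A simulation of 722 + 450 patients over 3 years gave 6.3% at the mid-range shares and 8.0% at 20% and 35%. Stage-stratified and within-stage tests stayed between 4.9% and 5.5%.

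**3. Bias from T or N category within a stage.** The article gives no figures for this, so the inputs are assumptions: a factor with hazard ratio h, present in 40% of stroma-high and 20% of stroma-low patients, and no TSR effect.

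Spurious HR = [1 + 0.4(h−1)] / [1 + 0.2(h−1)], which is 1.4/1.2 = 1.17 for h = 2 and 1.8/1.4 = 1.29 for h = 3.

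Log-rank mean = √(events × a(1−a)) × ln(spurious HR):

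- p-stage II (114 events, a = 0.225): 4.46 × 0.154 = 0.69, rejection 11%; 4.46 × 0.251 = 1.12, rejection 20%.
- p-stage III (97 events, a = 0.325): 4.61 × 0.154 = 0.71, rejection 11%; 4.61 × 0.251 = 1.16, rejection 21%.

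Over a wider set of assumed imbalances (10 to 20 percentage points, h = 2 to 3, shares 25% and 35%), the spurious HR runs from 1.09 to 1.33 and rejection from about 7% to 27%.

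**4. Power of an adjusted test.** Let R² be the squared correlation of TSR with the T and N covariates within a stage (not given; assumed 0 to 0.20). Effective events are the planned events × (1 − R²), and power = Φ(√[events × (1−R²) × a(1−a)] × ln 2 − 1.960).

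- p-stage II, 114 events, a = 0.25: 89%, 88%, 86% and 82% at R² = 0, 0.05, 0.10 and 0.20.
- p-stage III, 97 events, a = 0.35: 90%, 89%, 87% and 83%.

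Holding the step 1 power instead would take 114 / 0.8 = 143 and 97 / 0.8 = 122 events at R² = 0.20. At the lower shares (20% and 30%) the same formula gives 84% and 88% at R² = 0, before any adjustment.

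**The case against.** The article never calls the log-rank test primary, and the success statement names no test; a significant adjusted Cox coefficient would satisfy it equally well. The Cox model comes directly after the log-rank sentence, and the sizing HR is of the kind such a model yields, so a TNM-adjusted model may well be intended. Covariate lists are commonly left to a full protocol or SAP, and neither is shown. Sizing by p-stage also points to analysis by p-stage, which removes the difference between stages II and III.

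Much of this stands. A reader might infer that success formally rests on an unadjusted log-rank test, or that the stages will be pooled without stratification. The article says neither.

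It does not dispose of the point. The article goes beyond silence on covariates: it names a test, and that test as described does not address the quantity the study was sized for. The Cox sentence does not connect the model to TNM or to the success statement. Analysis by stage still leaves T3 with T4 in stage II, and the T and N categories mixed in stage III, as the stage definitions in the inclusion criteria show.

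**Conclusion.** The point holds as a mismatch between the named test and the sized, TNM-adjusted effect. A significant log-rank result alone would not establish that TSR adds to TNM.

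Its size is only partly known. Stage mix is minor on the plan's own rates, and small beside the design HR of 2.0. Confounding by T or N category within a stage could matter more, but its 11% to 21% rests wholly on the assumed 40% versus 20% imbalance and h of 2 to 3. A reader might take that range as the trial's false-positive rate. The documents do not support this, since they give no association between TSR and T or N category. All rejection rates also assume a two-sided 5% level.

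The matter should be settled before analysis. If an unseen SAP already makes the adjusted effect primary, only the success statement needs aligning.

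**What to change.** In Part 2, Statistical Analysis, name as primary the test of the TSR coefficient in a Cox model fitted within each p-stage (or stratified by p-stage if the stages are pooled), adjusted for prespecified T and N categories. Within p-stage II, where N is N0 by definition, this means T category. Keep Kaplan-Meier curves and the log-rank test as supporting description. Reword the success statement in the Abstract, Conclusions, so that it refers to that adjusted effect.

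The cost is mainly wording, because T and N are already needed to assign p-stage. The downside is a modest loss of power if TSR correlates with T or N: about 82% to 90% with the planned events, for R² of 0 to 0.20 and the upper end of the stated stroma-high shares. Power would be lower at the lower shares, where the planned events already fall short of 90% without adjustment.
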